## Methods and design

### Participants

#### Inclusion criteria for survivors

Currently between 18 to 39 years of ageDiagnosed with a blood cancer or solid tumorReceived chemotherapyCurrently within 6 months of final chemotherapy treatmentStages I – IV including metastatic, IF patient is off chemotherapy treatment and stableEnglish speakingAccess to an electronic device (i.e. computer, tablet, smart phone) with in internet connection

#### Exclusion criteria for survivors

CNS or colorectal cancer tumor diagnosisRecipient of an allogenic stem cell transplantWomen who are pregnantHaving taken antibiotics within 1 month prior to fecal collectionDiagnosis of a significant cognitive or developmental delay that precedes cancer diagnosis (e.g. down syndrome, ASD)

#### Inclusion criteria for control participants

Currently between the ages of 18 to 39Be a sibling, individual cohabiting with the patient (e.g. roommate, partner), or close friendEnglish speakingAccess to an electronic device (i.e. computer, tablet, smart phone) with in internet connection

#### Exclusion criteria for control participants

Having taken antibiotics within 3 months prior to fecal collectionPersonal history of cancerCurrent diagnosis/medication treatment for anxiety and/or depressionDiagnosis of irritable bowel syndrome/diseaseWomen who are pregnantDiagnosis of a significant cognitive or developmental condition (e.g. down syndrome, ASD)

##### Sample size and power

Target sample sizes of at least *n* = 50 cancer survivors and *n* = 50 healthy controls were selected based on sample sizes from previous studies on gut microbiota in cancer patients [17, 18] and practical considerations given the timeline and availability participants. With this sample size (*n* = 100 total), a medium effect size for group differences (Cohen’s d = 0.5, estimated with a power of 0.80, alpha = 0.05) can be detected using a one-sided test of the primary hypothesis that cancer survivors will have lower alpha diversity relative to controls [46].

##### Recruitment

Participants will be recruited in Calgary, Alberta from the Tom Baker Cancer Center, via social media and local advocacy groups, and by mail-out through the Alberta Cancer Registry. Patient referral and consent to contact forms will be provided to oncologists. Recruitment posters will be posted at relevant sites, and a digital copy of the poster will be shared on social media platforms.

### Demographics and clinical data

Clinical and demographic factors including current age, age at diagnosis, income, occupation, ethnicity, education, living arrangements, cancer diagnosis and treatments received, history of treatment related mucositis, current diet and exercise regimes, bowel habits, glucocorticoid medication, antibiotic, and probiotic use within the last 2 years, smoking, birth delivery mode (i.e. caesarian section vs. vaginal), and breastfeeding during infancy will be collected as these variables are known to impact the gut microbiota.

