### Cancer in young adults

The incidence of cancer among young adults has dramatically increased in recent decades [10], with over 8000 young Canadians diagnosed annually [12]. Between 1992 and 2013 the incidence of cancer has increased among young Canadian’s aged 15 to 29 by 18.2, and 11.9% among 30 to 39 year olds [12]. Considering their age at diagnosis, young adults experience unique personal, physical, and socioeconomic challenges throughout their cancer experience [12, 13]. As most young adult survivors are exposed to toxic therapies (e.g. chemotherapy) many will face years of chronicity living with treatment-related physical and psychosocial side-effects. For instance, Asher [14] reports that executive functioning, attention, concentration, processing speed, reaction time, motor speed and dexterity were the cognitive domains most frequently associated with chemotherapy induced cognitive impairment in all cancer populations. Additionally, Seitz et al. [15] examined the prevalence of posttraumatic stress, depression and anxiety among young adult survivors (*n* = 820) of adolescent cancer with a mean current age of 30.4 years [15]. They found that 90.5% cancer survivors had received chemotherapy, and 22.4% reported clinical symptoms of posttraumatic stress, anxiety and/or depression compared to only 14.0% of controls [15]. Posttraumatic stress symptoms in both male and female survivors were found to be more than three times that of controls [15]. Furthermore, female survivors reported symptoms of depression and anxiety significantly more often than controls, and 24.3% of the survivors met DSM-IV criteria for at least one mental disorder, relative to only 15.3% of the controls [15]. Indeed, the increased prevalence of young adult cancers in conjunction with the improved survival rates has resulted in a large group of survivors facing years of chronicity, unique challenges, and specific needs emerging from their cancer experience.

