### Data analysis

*Objective 1* will examine whether chemotherapy is related to long-term gut dysbiosis as indicated by reduced alpha diversity in patients relative to controls, and from time points 1 through 3. Gut microbiota alpha diversity will be evaluated with the Shannon and Chao1 indexes using QIIME. To further examine differences in bacterial composition between the groups, LEfSe (linear discriminant analysis effect size) will be used to evaluate differential abundance between patients and controls, allowing us to identify the key bacteria that contribute most to the chemotherapy group having different bacteria relative to healthy controls. Linear Mixed Modelling (LMM) analyses will be used to examine differences across time and between groups. Group (survivors vs. healthy controls) and time (T1 – T3) will be fixed factors and individual subject will be a random factor.

*Objective 2* will first test group differences in gut microbiota, cytokines, LPS, 5-HT and BDNF, cortisol, and body composition using LMM as described above. We will test the interplay between the physiological systems of our model by examining associations between the gut microbiota, cytokines, LPS, 5-HT and BDNF, cortisol, and body composition using univariate correlations. Then multivariate regression models regressing cytokines, cortisol and body composition on gut microbiota diversity will be conducted, including variables that showed significant univariate correlations in the modelling. Covariates included theoretically based on the literature will include type of cancer diagnosis (i.e. blood or solid tumor), history of mucositis, glucocorticoid medication, antibiotic, and probiotic use, birth delivery mode, and breastfeeding in infancy.

*Objective 3* will first test group differences in cognitive and psychological parameters, gut microbiota diversity, and levels of 5-HT and BDNF using LMM as described above. We will test the relationships between gut microbiota, 5-HT and BDNF, and cognitive and psychological parameters using univariate correlations. Then multivariate regression models regressing psychological and cognitive parameters on gut microbiota diversity will be conducted, including variables that showed significant univariate correlations in the modelling. Covariates included theoretically based on the literature will as specified in objective 2.

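### Sex and age are in neither the survivor-control models nor the Objective 2-3 covariate list, and sex is not among the listed variables, although controls are not stated to be matched on either

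*Protocol article*

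**What the plan says.** **Variables recorded.** The Demographics and clinical data section lists "Clinical and demographic factors including current age, age at diagnosis, income, occupation, ethnicity, education, living arrangements", continues through treatment and lifestyle items, and closes with "and breastfeeding during infancy will be collected as these variables are known to impact the gut microbiota". Current age is on the list. Sex and gender are not.

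**Group comparisons.** Under Data analysis, Objective 1, the linear mixed model is specified as follows: "Group (survivors vs. healthy controls) and time (T1 – T3) will be fixed factors and individual subject will be a random factor". Objectives 2 and 3 reuse that model for biomarkers, body composition, psychological and cognitive outcomes.

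**Association models.** For the Objective 2 regressions the section states: "Covariates included theoretically based on the literature will include type of cancer diagnosis (i.e. blood or solid tumor), history of mucositis, glucocorticoid medication". The remaining named items are antibiotic use, probiotic use, birth delivery mode and infant breastfeeding. Objective 3 takes the same list. Neither sex nor age is on it.

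**Objective 4.** The outcomes are regressed on the clinical and demographic factors of the survivors. By the data list, those factors include current age.

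**Controls.** The inclusion criteria admit a sibling, someone living with the patient (a partner or roommate, for example) or a close friend, aged 18 to 39 like the survivors. No matching on sex or on age within that range is stated.

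**The concern.** This is a non-randomised comparison, so the group coefficient carries any difference between survivors and controls in a factor that also affects the outcome. Partners are an expected source of controls and will often be of the other sex. If one sex predominates among survivors, the control group can lean the other way. For an outcome that depends on sex, the mixed model as written would then report part of that difference as an effect of chemotherapy.

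Fat mass, lean mass, body fat percentage and bone mineral are the planned outcomes most exposed to this. That they differ by sex is general knowledge and is not stated in the article. Even when the sex mix is equal in the two groups, leaving sex out puts its variance into the residual and costs power. In the Objective 2 and 3 regressions, sex and age could each be related both to gut diversity and to the outcome.

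The article says that the factors on its list are recorded because they affect the gut microbiota. Current age is on that list, yet it has no place in the survivor-control models.

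**Working it through.** **1. The plan's own figure.** The Sample size and power section gives "50 cancer survivors and *n* = 50 healthy controls were selected based on sample sizes from previous studies", with "d = 0.5, estimated with a power of 0.80, alpha = 0.05", for a "one-sided test of the primary hypothesis that cancer survivors will have lower alpha diversity relative to controls". At 50 per group, d = 0.5 and one-sided alpha 0.05, power is 0.804 by the normal approximation and 0.799 by the t-test. The stated 0.80 is reproduced and is not in dispute. The two-sided t-test power at the same n and d is 0.70, which is the reference for step 2.

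**Assumptions for steps 2 and 3.** The documents give neither a sex effect nor an expected sex mix. Let D be the difference between men and women in within-sex SD. For body composition D is taken as 1.0 to 2.0, and for outcomes weakly related to sex as 0.3 to 0.5. Each calculation uses one visit, 50 per group and independent groups.

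**2. Precision when the sex mix is balanced (half of each group female).**

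SD inflation = sqrt(1 + D² × 0.5 × 0.5) = sqrt(1 + 0.25 D²). A true within-sex d of 0.5 shrinks to 0.5 divided by this factor. Power is the two-sided t-test at 5%.

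| D | SD inflation | Effective d | Power (0.70 without inflation) |
|---|---|---|---|
| 1.0 | 1.12 | 0.447 | 0.60 |
| 1.5 | 1.25 | 0.400 | 0.51 |
| 2.0 | 1.41 | 0.354 | 0.42 |

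**3. Bias when the sex mix differs by 20 points (60% against 40% female, no true group effect).**

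Shift in within-sex SD = 0.2 × D. An unadjusted analysis uses the marginal SD, which here is sqrt(1 + D² × 0.6 × 0.4) = sqrt(1 + 0.24 D²). The spurious d is the shift divided by that SD. The standard error of d is about sqrt(2/50) = 0.2. Rejection is for a two-sided 5% test by the normal approximation.

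| D | Shift (within-sex SD) | Marginal SD | Spurious d | Rejection rate |
|---|---|---|---|---|
| 0.3 | 0.06 | 1.011 | 0.06 | 6% |
| 0.5 | 0.10 | 1.030 | 0.10 | 8% |
| 1.0 | 0.20 | 1.114 | 0.18 | 15% |
| 1.5 | 0.30 | 1.241 | 0.24 | 23% |
| 2.0 | 0.40 | 1.400 | 0.29 | 30% |

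A 40-point gap (70% against 30%) gives a spurious d of 0.36 to 0.59 for D from 1.0 to 2.0, and 0.12 to 0.20 for D from 0.3 to 0.5.

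**4. Where age enters.** Age is a listed demographic factor, so the Objective 4 regressions cover it. Those regressions use survivors only and contain no group term, so they leave the Objective 1 to 3 contrasts unadjusted. No age effect is quantified here, because the documents give no basis for one.

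**The case against.** **Condensed article.** An article shortens the full protocol, and covariates are often left to an analysis plan. The covariate sentence is also phrased as an inclusion, and the abstract mentions covariates in general terms. This has some force, but the article does not stay silent. It writes out the fixed effects of the mixed model and names seven covariates, down to delivery mode and breastfeeding. What is stated omits sex and age.

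**Sex may be recorded anyway.** A reader might infer that sex will not be collected. The text does not support that. The list is introduced as a set of examples, and pregnancy is an exclusion criterion in both groups, so screening has to touch on sex. All that can be said is that sex is not listed.

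**Age is used somewhere.** A reader might infer that age is in no regression at all. That would be wrong, because Objective 4 covers it among survivors. The shared 18-39 range also limits age confounding, though it does not remove it.

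**The background on mood.** A reader might take "female survivors reported symptoms of depression and anxiety significantly more often than controls" as evidence that mood differs between women and men. That sentence compares female survivors with controls. It may hint that the survivor-control difference varies by sex, but it does not show the main effect of sex that this kind of confounding needs.

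**The size depends on the outcome.** The large figures apply to body composition under assumed sex effects. The primary hypothesis concerns alpha diversity, for which the documents give no sex effect. If that effect is small, the bias is minor. Opposite-sex partners also create no imbalance when survivors are themselves half female. Both points stand.

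**Conclusion.** The point holds in a limited form. The survivor-control models of Objectives 1 to 3 and the named covariates of the Objective 2 and 3 regressions contain neither sex nor age. No matching makes up for this, and Objective 4 cannot.

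The consequence is material for body composition if the sex effect is 1 to 2 within-sex SD. A 20-point gap in percent female then gives a spurious d of about 0.18 to 0.29 against a design effect of 0.5, and balanced groups lose 0.10 to 0.28 of power (0.70 to 0.60, and 0.70 to 0.42). With sex effects of 0.3 to 0.5 SD, the same gap gives a d of 0.06 to 0.10 and rejection rates of 6% to 8%.

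The sex effects and the sex mix are assumptions. The calculation does not show that the alpha-diversity comparison is seriously biased, and it says nothing about the size of any age effect. The change is worth making because the remedy costs almost nothing.

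**What to change.** - Name sex among the collected variables in the Demographics and clinical data section.
- Add sex and age as fixed effects to the survivor-control mixed models of Objectives 1 to 3 and to the Objective 2 and 3 regressions.
- Include sex among the demographic factors of Objective 4, where age already belongs.
- Report the unadjusted group differences beside the adjusted ones.

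The cost is two model degrees of freedom, plus one form field if sex is not already recorded. No visit, sample or procedure is added.

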### Gut microbiota profiling

Investigators will provide participants with a stool collection kit and instructions for collecting samples. Stool samples will be collected into a sterile conical tube and placed in a biohazard bag that will be stored in the participant’s freezer until the date of their appointment (up to 3 days). Samples will be brought to the University of Calgary on ice and stored at − 80 °C until processed. Microbial profiling will be carried out according to our previously published protocol [42]. Bacterial DNA will be extracted from stool samples using a FastDNA spin kit for feces (MP Biomedicals, Santa Anna, CA, USA) and the V3-V4 region sequenced by the Centre for Health Genomics and Informatics (University of Calgary) using the Illumina 16S rRNA sequencing platform. Sequencing data from MiSeq will be demultiplexed and converted to fastq format using Illumina’s bcl2fastq software. Primers will be removed from reads using CutAdapt and initial quality trimming performed. Following primer removal, length sequences of shorter than 10 base pairs will be removed, and the quality trimming threshold set at Q20. R package DADA2 will be used for sequence/OTU clustering. Chimeric sequences will then be removed, and taxonomic assignment performed using the RDP classifier and RDP database as reference. Further downstream analysis will be performed using Phyloseq R package. The Shannon and Simpson index will be used to measure alpha diversity. Non-metric multidimensional scaling (NMDS) on Bray-Curtis dissimilarity matrix will be used to evaluate beta diversity. Differential abundance analysis between groups will be carried out using the LEfSe algorithm [47], with an alpha = 0.05 to determine significance of differentially abundant features.

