### Present study

#### The objectives of the present study are to investigate

i.Whether chemotherapy is related to long-term attenuation of gut microbiota alpha diversity (i.e. gut dysbiosis, and which species differ significantly between patients and healthy controls);ii.Associations between gut microbiota, body composition (i.e. fat mass and lean mass, body fat percentage, and bone mineral concentration), inflammatory cytokine biomarkers (IL-6, IL-1B, TNF-a, IL-10), C-reactive protein (CRP), lipopolysaccharide (LPS), serotonin (5-HT), brain derived neurotrophic factor (BDNF), and cortisol;iii.Associations between gut microbiota, and psychological and cognitive outcomes including anxiety, depression, PTSD symptoms, pain, fatigue, and social and cognitive functioning;iv.Relationships between demographic and clinical factors, gut microbiota, and physiological, psychological and cognitive outcomes for survivors.

We hypothesize that:
i.Chemotherapy will be associated with significant reductions in gut microbiota alpha diversity at all time points, and relative to healthy controls;ii.Gut dysbiosis will be associated with increased risk for overweight/obesity, elevated pro-inflammatory cytokines, CRP and LPS, reduced serotonin and BDNF, and augmented levels of cortisol in survivors;iii.Gut dysbiosis will be associated with increased anxiety, depression, PTSD symptoms, pain, fatigue, and social and cognitive deficits in survivors;iv.There will be relationships between certain clinical factors (e.g. mucositis, antibiotic use), gut microbiota alpha diversity, and physiological, psychological and cognitive outcomes.

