### Procedure

Once identified, participants will be contacted by telephone or email to further verify inclusion and exclusion criteria, to obtain written informed consent, and schedule their first appointment. We will aim to assess participants at 3 different time points: < 2 months (T1), 3/4 (T2) and 5/6 (T3) months post chemotherapy, with healthy controls ideally being tested on the same day or within 5 days from when the patient is tested.

Participants will then receive a package via mail or in person, with instructions and materials for stool sample collection, and a link to fill out the self-report questionnaires, and demographic and clinical data online using REDCap. REDCap is a free, secure, browser-based application designed to support Electronic Data Capture for research studies provided through the Clinical Research Unit in the Cumming School of Medicine at the University of Calgary. Medical charts will also be accessed to confirm information regarding cancer diagnosis, treatment, glucocorticoid and antibiotic medication use, and mucositis.

Participants will be instructed to collect stool samples at home which can be stored in a freezer up to 3 days prior to their appointment, and to complete their online questionnaires prior to the appointment. On the day of their appointment, we will collect their stool sample from them. Participants will then be taken to have a hair sample collected for cortisol analysis (approximately 10 min), complete the cognitive task (i.e. the SART) on a computer (approximately 6 min), and complete their DXA scan (approximately 10 min), and have their blood drawn for serum biomarker analyses (approximately 10 min). This whole process should take approximately 45 min. Participants’ T2 and T3 month follow-up appointments will be scheduled at each subsequent visit and the procedure will be the same with respect to psychological and cognitive measures completed online, followed by their in person testing and biological sample collection. Participants will be provided a voucher for parking, and may choose from compensation in the form of either $30 at the end of the study or a pass to a fitness class after each appointment (they will have options to choose from in advance). If desired, participants will also receive a package with their individual results summarized and interpreted at the end of the study.

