## Conclusion

Knowing what bacterial species are depleted after chemotherapy, how long these effects last, and the physiological mechanisms that may drive psychological and cognitive issues among survivors is a crucial step forward in gut microbiota and young adult cancer research. Understanding the bio-behavioural mechanisms that drive psychological and cognitive dysfunction among survivors will allow for tailored interventions to be developed. Future studies can aim to aid cancer patients and survivors by co-administering specific health promoting bacteria (i.e. probiotics), with the potential of preventing or reversing physical and mental health issues that many young survivors face.

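### Differentially abundant taxa are declared by LEfSe at 0.05 per feature with no stated false discovery control, so the false share of the reported list is not controlled

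*Protocol article*

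**What the plan says.** In the protocol article, the section Gut microbiota profiling names LEfSe for the comparison of taxa between groups, "with an alpha = 0.05 to determine significance of differentially abundant features". Under Data analysis, Objective 1 repeats the choice: "LEfSe (linear discriminant analysis effect size) will be used to evaluate differential abundance between patients and controls". The stated purpose there is to find the taxa that account most for the difference between the two groups. The question it serves is in the objectives: "which species differ significantly between patients and healthy controls". Neither section states a correction across taxa, an effect-size cut-off, or the visit whose samples enter LEfSe.

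The Procedure section plans three visits ("We will aim to assess participants at 3 different time points"), and each control is a sibling, cohabitant or close friend of a patient. The random subject effect belongs to the linear mixed model, and no taxon is named as an outcome of that model. The listed covariates belong to the regressions of Objectives 2 and 3. Objective 4 does take species composition as an outcome, but only against survivors' own clinical and demographic factors, so it does not adjust the survivor–control contrast.

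On use, the Conclusion opens with "Knowing what bacterial species are depleted after chemotherapy, how long these effects last" and goes on to tailored interventions and probiotics. The Discussion calls the study exploratory and expects larger studies to follow.

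**The concern.** A threshold of 0.05 applied to each feature limits the error for one taxon, not for the list. The list is what gets reported and what would guide the choice of bacteria for later work. When many taxa are screened, some pass by chance, and the plan as published gives the reader no means of judging how many. Objective (i) asks for species that differ significantly, so the list will be read as a set of findings and not only as a picture.

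A second, smaller issue concerns interpretation. Survivors may have taken antibiotics up to 1 month before a stool sample, controls not within 3 months (exclusion criteria for each group). The section Demographics and clinical data counts antibiotic use among the factors known to affect the microbiota. A plain two-group comparison cannot separate that built-in difference from chemotherapy, and multiplicity control does not remove it.

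**Working it through.** **The plan's own figure.** The article gives no figure for false-positive taxa. Its only power figure is for alpha diversity (Sample size and power): d = 0.5, 50 per group, one-sided 0.05, power 0.80. It reproduces: Φ(0.5 × √(50/2) − 1.645) = Φ(0.855) = 0.804 (0.799 with the t distribution). It does not extend to individual taxa.

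**Expected false taxa.** Inputs: alpha = 0.05 per feature (stated); number of taxa m (assumed, not given); all taxa null and tests independent (assumed). Expected false = m × 0.05. About half, m × 0.025, would point to depletion. P(at least one) = 1 − 0.95^m. P(three or more) is the binomial tail.

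| m (assumed) | Expected false | of which depletions | P(≥ 1) | P(≥ 3) |
|---|---|---|---|---|
| 20 | 1.0 | 0.5 | 64% | 8% |
| 50 | 2.5 | 1.25 | 92% | 46% |
| 100 | 5 | 2.5 | 99.4% | 88% |
| 200 | 10 | 5 | > 99.9% | 99.8% |

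**Share of the list that is false when some taxa do differ.** With a fraction π truly different and power w per taxon (both assumed), the share is approximately (1 − π) × 0.05 / [(1 − π) × 0.05 + π × w].
- π = 0.10, w = 0.5: 0.045 / (0.045 + 0.050) = 47%.
- π = 0.20, w = 0.8: 0.040 / (0.040 + 0.160) = 20%.

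This share does not depend on m. Benjamini-Hochberg at q = 0.05 would hold the expected share to about 5% or less.

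**Pairs.** The feature test was taken as a two-group rank test (an assumption, since the article does not describe the inner steps of LEfSe) and simulated with 50 per group and 10,000 runs. Per-taxon error was 0.052 with unrelated groups, 0.027 with pair correlation 0.2 and 0.014 with 0.4. Ignoring positively correlated pairs makes the test conservative.

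**Repeat visits.** If three visits are pooled as if independent, the variance is understated by a factor 1 + 2ρ, where ρ is the within-person correlation (assumed). The error becomes 2 × [1 − Φ(1.96/√(1 + 2ρ))]:
- ρ = 0.3: 1.96/√1.6 = 1.55, error 12% (simulated 12%).
- ρ = 0.5: 1.96/√2.0 = 1.39, error 17% (simulated 16%).
- ρ = 0.7: 1.96/√2.4 = 1.27, error 21% (simulated 20%).

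With a pair correlation of 0.2 in the person-level component, the simulated values fall to 10%, 13% and 17%. If each visit is tested separately instead, the chance of a false call for a taxon at any of the three is 11% to 14%. At one visit alone it stays at 5%.

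**The case against.** The best defence is that this is a condensed article. A correction across taxa, an effect-size cut-off and the choice of visit may all stand in a fuller plan, and nothing in the article rules them out. The study is also called exploratory, the one powered hypothesis concerns alpha diversity, and the probiotic work is placed in future studies. The exploratory label does lower the stakes. The point about condensation carries less weight, because the article does not simply leave the matter open: it gives a method and a significance level for declaring features. An effect-size cut-off, if one exists, could shorten the list, but it would not by itself control an error rate.

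Three stronger readings are tempting, and the article does not support them:
- A reader might infer that several of the bacteria called depleted are bound to be false. The number of taxa is unknown, the counts above assume every taxon is null, and about half of false calls would be increases. With 20 to 50 taxa, the expected number of false depletions is only about one or fewer.
- A reader might infer that ignoring the pairs produces false taxa. It does the reverse and costs power.
- A reader might take 12% to 21% as the actual per-taxon error. That holds only if the visits are pooled, which no section says.

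It is also fair to say that replacing LEfSe altogether with mixed models for each genus would be partly a matter of preference, and would move the question from species to genus.

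**Conclusion.** The concern holds for the decision rule as published: 0.05 per feature, no stated false discovery control, and LEfSe as the only named comparison of individual taxa between the groups. The size depends on an unstated number of taxa. Under the global null it is 2.5, 5 or 10 expected false declarations for 50, 100 or 200 taxa. If 10% to 20% of taxa truly differ with power 0.5 to 0.8 each, 20% to 47% of the list would be false. Inflation from repeat visits is conditional on how the visits are used, and the pairing affects power only. The primary hypothesis on alpha diversity is untouched. The rule should be changed before the taxon list is produced, because the list answers part of objective (i) and is put forward as a basis for interventions.

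**What to change.** 1. State that the per-feature p-values are adjusted by Benjamini-Hochberg and that taxa are declared at q < 0.05, over a taxon set fixed in advance by a prevalence filter applied without reference to group.
2. Name the one visit at which LEfSe is run.
3. Label the resulting list exploratory wherever it is reported.
4. As a sensitivity analysis, check the declared taxa in a mixed model with group and time, random effects for subject and dyad, and adjustment for recent antibiotic use. An indicator for use in the 3 months before the sample is workable. Under the eligibility rules only survivors can have it, so the group contrast then rests largely on samples without such use.

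The article already plans to collect antibiotic use and to confirm it from charts, so no new data are needed. The costs are a shorter list of significant taxa, some power lost by using one visit for the main list, and modest extra analysis.

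Suggested wording: LEfSe will compare survivors and controls at [named visit]; p-values will be adjusted by the Benjamini-Hochberg method over all taxa passing the prespecified prevalence filter, and taxa with q < 0.05 will be reported as exploratory findings.
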